### 2.2. Study Objectives

The primary clinical objective is to estimate the 6-month cumulative incidence of at least one toileting-related fall among participants managed through the pathway; this is an estimate of event occurrence, not causal effectiveness.

The secondary clinical objectives are to characterize nighttime and total falls and changes in urinary symptoms, nocturia, mobility, and functional independence. The implementation objectives are to assess the reach, adoption, delivery, fidelity, follow-up, data quality, and safety.

We hypothesize that the standardized pathway can be implemented consistently across levels of care, as assessed by the prespecified RE-AIM and fidelity measures. The clinical outcomes will be exploratory and will not be interpreted as confirmatory evidence of effectiveness.

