## 2. Materials and Methods

### 2.1. Study Design and Setting

This multicenter, prospective, single-arm interventional implementation study will be conducted at 15 Chinese centers representing different levels of healthcare delivery: four tertiary Grade A hospitals, five secondary hospitals, and six primary-level hospitals. Chinese PLA General Hospital is the coordinating center.

The participating centers must have access to the target population; a designated local study team, the capacity to complete standardized multidimensional assessment and longitudinal follow-up; the ability to deliver or coordinate the core intervention domains; and the capacity to comply with common training, case report forms, fall surveillance, data quality, safety reporting, and ethical requirements. These minimum operational requirements are intended to preserve a common implementation standard across settings.

Including different levels of care is intentional and will allow for evaluation under real-world variations in case mix, staffing, rehabilitation capacity, equipment, and service organization. All centers will use the same eligibility criteria, assessment and intervention-assignment framework, outcome definitions, monthly fall surveillance schedule, documentation, training, and safety procedures. Specific intervention modalities may vary with participant-level clinical indications and local resources, but the underlying assessment and decision framework will remain standardized.

All participants will enter the same integrated pathway. There is no concurrent control arm, treatment allocation, or masking because the interventions are assigned based on a prespecified risk assessment and clinical indications.

The pathway comprises screening and consent, standardized baseline assessment; risk stratification; individualized multicomponent care; monitoring; reassessment; and adjustment according to response, adherence, safety, and changing risk. The follow-up will last 6 months (Figure 1; Table 1).

Figure 1 summarizes the screening, baseline assessment, risk stratification, individualized multicomponent intervention, monitoring and adjustment, 6-month outcome assessment, and integrated clinical and RE-AIM evaluation.

The protocol follows relevant prospective study-reporting principles and SPIRIT guidance [15,16].

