### 2.14. Sample Size and Enrollment Target

A total of 300 participants are planned to be enrolled, consistent with the registered target. This target refers to participants enrolled and does not imply that all 300 will necessarily have evaluable 6-month outcome data because some loss to follow-up is anticipated.

Because the study is primarily designed to evaluate implementation of a complex individualized pathway rather than superiority of a single treatment against a concurrent control group, no treatment-effect-based sample size calculation was used. The pragmatic target supports multicenter implementation and reasonably precise estimation of key proportions. For an evaluable sample of 300, a simple binomial approximation gives a maximum 95% confidence interval half-width of about 5.7 percentage points for a proportion near 50%, with narrower intervals farther from 50%.

No cluster design effect inflation was applied because this is not a cluster-randomized comparative trial and a reliable intraclass correlation is unavailable. Center clustering will instead be addressed in the prespecified analyses, with center-specific estimates reported descriptively.

With a 10%, 15%, or 20% loss to follow-up, approximately 270, 255, or 240 participants would remain evaluable, corresponding to maximum 95% confidence interval half-widths of about 6.0, 6.1, or 6.3 percentage points for a proportion near 50%.

The numbers enrolled, completing follow-up, and included in each analysis will be reported with reasons for loss or non-evaluability. Center and subgroup analyses will be descriptive, not separately powered tests of differential effectiveness.

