Potential center effects will be examined explicitly. The primary cumulative incidence estimate and key implementation outcomes will first be reported for the overall cohort, with center-specific estimates and confidence intervals presented descriptively. When a clustering adjustment is required, the center will be incorporated as a random intercept if a stable estimation is possible. If not, it will be included as a fixed categorical effect where feasible; otherwise, center-specific descriptive estimates will be used. The center findings will characterize implementation heterogeneity and will not be formal rankings of institutional performance.

The implementation and fidelity indicators will also be summarized by center type to characterize the variation across levels of care, without inferring differential effectiveness.

Exploratory multivariable models will use covariates prespecified a priori on clinical grounds rather than data-driven stepwise selection: age, sex, baseline fall history, comorbidity burden, baseline functional status, caregiver support, recruitment setting, baseline urinary symptom status, and predominant disability/functional impairment profile. Model complexity will be limited according to sample size and available event counts to reduce overfitting; participating centers will be included as a random intercept when stable estimation is possible.

Prespecified subgroup analyses will examine age (18–64 vs. ≥65 years), predominant impairment profile (physical/mobility, cognitive, or mixed/multidomain), recruitment setting, baseline urinary symptoms, and functional dependency. Subgroup estimates will include 95% confidence intervals; regression-based heterogeneity analyses will be exploratory when data permit, with no claims of differential effectiveness.

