## 3. Expected Results

The study is expected to determine whether the integrated pathway can be delivered consistently across participating settings and to quantify the enrollment, assessment completion, risk-matched intervention delivery, fidelity, follow-up completion, data completeness, and intervention-related adverse events. It will also provide prospective estimates of 6-month toileting-related fall occurrence and within-participant changes in urinary symptoms, nocturia, mobility, balance, and independence in activities of daily living. Because there is no concurrent control group, clinical changes will be interpreted as exploratory and hypothesis-generating rather than evidence of causal effectiveness.

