## 4. Discussion

This protocol addresses toileting-related falls as a multidimensional clinical and care-delivery problem rather than as an isolated mobility event. By integrating urinary symptoms, gait and balance, physical function, psychological/cognitive factors, caregiver support, and environmental hazards within one decision pathway, the program is intended to reduce fragmentation between disciplines that commonly manage these risks separately. The approach is particularly relevant to people with disability or care dependency, in whom several modifiable risks may coexist and change over time. Recent longitudinal evidence from residential care also suggests that changes in mobility, supervision, activity, and care conditions can accompany changes in fall occurrence, reinforcing the importance of the care environment when interpreting fall risk [28].

A major strength of the study is its prospective multicenter implementation focus. Standardized assessment, risk stratification, intervention assignment criteria, documentation, training, and quality control procedures are combined with flexibility in the intervention package so that care can be adapted to individual clinical indications and local resources. The RE-AIM-informed evaluation will provide information not only on clinical events and functional changes but also on the reach, adoption, intervention delivery, fidelity, follow-up, data quality, and safety. Together with the center-level implementation measures, these data should help identify which elements of the pathway are reproducible across settings and which require local adaptation.

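### The study expects to determine whether the pathway is delivered consistently across levels of care, but it plans only separate descriptive summaries by center and center type and no comparison of levels

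*Protocol article*

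**What the plan says.** The hypothesis appears in section 1 (last paragraph) and again in section 2.2: "We hypothesize that the standardized pathway can be implemented consistently across levels of care, as assessed by the prespecified RE-AIM and fidelity measures". Section 3 describes what the study will deliver: "The study is expected to determine whether the integrated pathway can be delivered consistently across participating settings". Section 4 adds that "these data should help identify which elements of the pathway are reproducible across settings and which require local adaptation".

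The levels compared are "four tertiary Grade A hospitals, five secondary hospitals, and six primary-level hospitals" (section 2.1).

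On analysis, section 2.10 has the consistency indicators summarized for each center and, where informative, by center type. Section 2.15 gives center-specific estimates with confidence intervals. It adds a center random intercept if a clustering adjustment is needed and the fit is stable, with a fixed center effect as fallback. Indicators by level are "summarized by center type to characterize the variation across levels of care, without inferring differential effectiveness". Section 2.14 calls center and subgroup analyses descriptive and not separately powered, and section 4 says center and center-type findings are not confirmatory.

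Section 2.14 gives precision for the whole cohort only: half-widths of 5.7 points at 300 evaluable, and 6.0, 6.1 and 6.3 points when "approximately 270, 255, or 240 participants would remain evaluable".

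**The concern.** Consistency across levels of care is a statement about differences between levels and variation between centers. The planned output is a set of separate proportions. None of the stated analyses estimates a level difference, and although a random-intercept fit would produce a between-center variance, nothing says it will be used to judge consistency. The stated conclusion, to determine whether consistency holds, is therefore stronger than the descriptive analysis offered for it.

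What is at stake is the main implementation conclusion and the sorting of pathway elements into those that transfer and those that need local adaptation. With few centers per level and few participants per center, both could rest on sampling noise or on how a reader chooses to look at the table.

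**Working it through.** **Inputs from the article.** 300 participants; 15 centers, of which 4 tertiary, 5 secondary and 6 primary; two-sided 95% intervals.

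**Assumptions, because the article gives no figure.** Equal enrollment of 300/15 = 20 per center, hence 80, 100 and 120 by level; true indicator rates of 80% to 90%; ICC 0 to 0.10.

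**1. The article's own precision.** Half-width = 1.96 × √(0.25/n).
- n = 300: 5.66; n = 270: 5.96; n = 255: 6.14; n = 240: 6.33 points.
- These reproduce the stated 5.7, 6.0, 6.1 and 6.3.

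**2. The same formula at the units the hypothesis concerns** (no clustering).
- By level at 50%: 11.0 (n = 80), 9.8 (n = 100) and 8.9 (n = 120) points.
- For one center of 20: 21.9 points at 50%, 17.5 at 80%, 13.1 at 90%.

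**3. Chance spread among identical centers.** Simulation of 15 centers, each binomial with n = 20 and the same true rate; the statistic is the highest minus the lowest center proportion.

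| True rate in every center | Median range | 5th to 95th percentile | Range of 20 points or more |
|---|---|---|---|
| 90% | 20 points | 15 to 30 | about 82% of runs |
| 85% | 25 points | 20 to 35 | about 95% |
| 80% | 30 points | 20 to 40 | about 99% |

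With real heterogeneity at ICC 0.05 and a mean rate of 90%, the median range is 30 points (20 to 45). That overlaps heavily with the no-heterogeneity row, so the raw range does not separate the two situations. For identical centers, the spread among the three level proportions reaches 5 points in roughly half to two thirds of runs at 90% to 80%. It reaches 10 points in about 5% to just under 20%.

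**4. What a direct level contrast would give.** Tertiary minus primary, center as the unit, both at 90%:
- Variance of a center proportion = 0.9 × 0.1/20 × (1 + 19 × ICC), that is 0.0045 at ICC 0 and 0.01305 at ICC 0.10.
- SE = √variance × √(1/4 + 1/6) = 0.0433 and 0.0737.
- With t on 4 + 6 − 2 = 8 df (2.306), the plug-in half-widths are 10.0 and 17.0 points. Averaged over simulated trials they are 9.7 and 16.0, because a small-sample SD is on average below the true SD. With 1.96 in place of t they are 8.5 and 14.5.

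So a half-width of about 10 to 16 points is what 15 centers can offer for this contrast.

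**5. How a true 90% versus 80% gap would look.** Tertiary (n = 80) against primary (n = 120), ICC 0 to 0.10:
- The two Wilson 95% intervals overlap in 68% to 81% of runs.
- The observed gap is below 5 points in only about 15% to 27% of runs.

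A reader who goes by overlapping intervals would usually call this consistent. A reader who goes by the point estimates would usually see a gap. The article does not say which reading applies.

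**The case against.** Much can be said for the plan. Section 2.3 describes the design as estimation-oriented and noncomparative, and sections 2.14, 2.15 and 4 label center and center-type findings descriptive. Section 2.15 plans confidence intervals by center, which display the noise, and says that center results are not rankings. Section 2.10 can be read as defining consistency by adherence to a common core protocol, not equality of rates. A statistical analysis plan is mentioned but not shown, and a numerical margin could sit there.

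Most of this stands, and it limits the point. The absence of a margin is not the finding. Three stronger readings that a reader might infer are not supported:
- That a real 10-point gap would usually look consistent. This holds only if overlapping intervals, or in most scenarios a non-significant test, are taken to mean consistency. The article states neither rule, and on point estimates the gap usually shows (step 5).
- That the summaries are purely raw. Confidence intervals and a conditional random intercept are planned.
- That no result could contradict the hypothesis. A very large gap between levels plainly would.

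What the objection does not remove is the mismatch within the article. The descriptive labels in sections 2.14 and 4 do not fit the claim in section 3 to determine consistency, and separate summaries do not estimate the quantity that the hypothesis is about.

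**Conclusion.** The point holds in limited form. The only hypothesis concerns consistency across levels of care, and the stated analysis neither contrasts the levels nor ties a between-center variance to that question. Chance alone would put a median of 20 to 30 points between the best and worst of 15 identical centers (true rates 90% to 80%), while the only precision quoted is about 6 points for the pooled cohort. The same table could support either conclusion.

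The sizes rest on equal enrollment of 20 per center, the assumed rates and, for the level contrast, an assumed ICC of 0 to 0.10. They apply to participant-level indicators only. Adoption and center maintenance are proportions of centers or personnel, and these calculations do not cover them. The mismatch between the claim and the analysis does not depend on any of these assumptions.

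**What to change.** In section 2.15, for the key participant-level indicators (risk-matched delivery, risk–intervention concordance, follow-up completion):
- Report the pairwise differences between levels of care with 95% confidence intervals that account for center.
- Report the between-center SD with its confidence interval from a random-intercept model.
- State that the raw range of center proportions is not read as heterogeneity.

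In sections 1, 2.2 and 3, replace hypothesizing or determining consistency with estimating variation between levels and between centers. This agrees with the estimation-oriented design in section 2.3.

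A margin for claiming consistency is optional, and useful only if the sponsor fixes it before enrollment. Section 2.18 reports that recruitment had not begun on 1 August 2026.

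The cost is a few sentences and a small analysis of data already to be collected. The downside is that with 15 centers the intervals will be wide, about 10 to 16 points either side for tertiary minus primary at 90%, so the study will be able to claim less about consistency than it now expects.

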### 2.3. Conceptual and Implementation Framework

The pathway assumes that toileting-related falls arise from interacting urinary, mobility/physical, psychological/cognitive, caregiver, and environmental risks rather than from a single disease process. These domains are assessed together so that intervention decisions target each participant’s dominant and modifiable risks and can be revised as those risks change.

Implementation evaluation will follow the RE-AIM framework [17]. The reach concerns entry of eligible individuals into the pathway; effectiveness comprises prespecified exploratory clinical and safety outcomes; adoption concerns center- and staff-level uptake; implementation concerns completion of assessment, delivery of risk-matched interventions, risk–intervention concordance, fidelity, documentation, and data completeness; and maintenance concerns 6-month follow-up completion and continued pathway delivery during the study period. Because the study is single-arm, the effectiveness outcomes will not be interpreted as comparative treatment effects.

Each RE-AIM domain is operationalized with prespecified measures, data sources, and time points. The design therefore combines clinical and implementation data while retaining the estimation-oriented, noncomparative nature of the protocol. Longer-term organizational maintenance beyond 6 months is outside the present study.

The RE-AIM definitions and measures are summarized in Table 2. Structured fall prevention programs, such as STEADI, support standardized training, workflows, risk assessment, and targeted intervention in routine care [18,19].

### 2.4. Participants

Eligible participants are adults at increased risk of toileting-related falls because of one or more interacting domains, including disability or functional limitation, loss of independence or care dependency, urinary symptoms, impaired mobility or balance, previous falls, cognitive or psychological problems, unsafe nighttime toileting, or environmental hazards.

The broad age range is intentional because the pathway is organized around a shared clinical problem—toileting-related fall risk—and common modifiable risk domains rather than a single diagnosis, disability type, or age group. Regardless of age, impairment profile, or recruitment setting, participants will undergo the same standardized baseline assessment, risk stratification process, outcome definitions, and follow-up procedures, while the intervention components will be individualized to identified risks. Prespecified subgroup analyses will explicitly characterize the age, functional, and setting-related heterogeneity.

Recruitment may occur in outpatient, inpatient, rehabilitation, long-term care, or community-linked services environments.

### 2.5. Eligibility Criteria

#### 2.5.1. Inclusion Criteria

Age 18 years or older, with no upper age limit.Presence of physical disability, functional limitation, loss of independence, or a need for assistance with activities of daily living.Presence of at least one risk factor for toileting-related falls, including but not limited to urinary frequency, urinary urgency, nocturia, urinary incontinence, voiding difficulty, overactive bladder, underactive bladder, impaired gait or balance, reduced muscle strength, fear of falling, cognitive or emotional problems, a history of falls, unsafe nighttime toileting, or toileting-related environmental hazards.Ability and willingness to participate in study assessments and follow-up procedures, with caregiver assistance when necessary.Written informed consent provided by the participant or, when applicable, a legally authorized representative.

#### 2.5.2. Exclusion Criteria

Acute infection or another acute medical condition requiring immediate treatment that would prevent participation in study assessments or interventions.A severe or unstable medical condition that, in the investigator’s judgment, would make participation unsafe or interfere materially with study procedures or follow-up.Severe disturbance of consciousness or another condition that would prevent completion of the required assessments and study procedures even with appropriate assistance.Inability to participate in the planned follow-up or provide sufficient study-related information.Any other condition that, in the investigator’s judgment, would make an individual unsuitable for participation.

### 2.6. Recruitment and Informed Consent

Recruitment is planned from 1 September to 31 December 2026 across all 15 centers. Investigators will explain study procedures, risks and benefits, alternatives, confidentiality, and voluntariness before obtaining written consent. When an individual’s capacity is insufficient, a legally authorized representative may consent in accordance with ethics requirements, with participant assent sought when feasible.

### 2.7. Multidimensional Baseline Assessment

The standardized baseline assessment will cover demographic characteristics, type and predominant profile of disability or functional impairment; comorbidities; recruitment setting; living arrangement; care dependency; previous falls; toileting-related circumstances; and the major urinary, mobility/physical, psychological/cognitive, caregiver, and environmental risk domains.

Key baseline covariates will be defined consistently across centers. Age will be recorded in completed years; recruitment setting as outpatient, inpatient, rehabilitation/long-term care, or community-linked services; baseline fall history as ≥1 fall in the previous 12 months; comorbidities as documented physician-diagnosed chronic conditions; and caregiver support as routine family, informal, or professional assistance with toileting, mobility, transfers, or activities of daily living. Baseline urinary symptom status and predominant disability/functional impairment profile will also be classified using standardized assessment.

Validated Chinese-language versions will be used for OABSS, PHQ-9, GAD-7, and FES-I, while POMA and MBI will follow standardized study procedures [20,21,22,23,24,25]. Because the cohort is clinically heterogeneous, each instrument will be administered only when its construct can be assessed validly according to prespecified applicability criteria. Protocol-defined non-administration will be documented separately from missing study data so that inapplicability is not treated as loss of information.

The urinary assessment will include symptom history, voiding records, nocturia frequency, urgency, urinary incontinence, voiding difficulty, and the clinically indicated PVR or Qmax. OABSS will be administered at baseline to participants with at least one storage symptom who can provide reliable self-reporting and be repeated at Month 6 when still applicable [20]. Participants with isolated voiding symptoms or an inability to provide reliable symptom self-reporting will not be required to complete OABSS; the reason for non-administration will be documented.

The physical assessment will include strength, joint mobility, transfers, sit-to-stand performance, gait, balance, mobility aids, and functional dependence. POMA will be performed at baseline and Month 6 in participants who can safely stand and ambulate, using habitual aids if needed; non-ambulatory or medically unsafe participants will not be tested [21]. MBI will assess activities-of-daily-living independence at baseline and Month 6 using participant, caregiver, and clinical information as appropriate [22].

The psychological/cognitive assessment will include fear of falling, anxiety, depressive symptoms, cognition, cooperation, and caregiver support. PHQ-9 and GAD-7 will be used at baseline when reliable self-reporting is possible [23,24]. FES-I will be used in participants able to self-report and who undertake standing, transfer, or ambulatory activities relevant to toileting [25]. Protocol-defined non-administration will be documented.

The environmental and care assessment will address nighttime lighting, bed-to-toilet route, floor hazards, thresholds, handrails, toilet height, bedside toileting devices, and caregiver response. The assessment–intervention–outcome matrix is shown in Table 3.

